**Discussion:**

The assessed outcomes will include stroke severity using National Institute of Health Stroke Scale (NIHSS) score, ability to perform activities of daily living using Barthel Index (BI) score, depression rate using Beck Depression Inventory (BDI-II) score, quality of life using EQ-5D-3L score, medication adherence using Modified Morisky Medication Adherence Scale (MMAS-8) score, patient satisfaction using Patient Satisfaction Questionnaire (PSQ) score and the number and type of complications in patients in two groups. These outcomes will be assessed at baseline, after two months and after three months from the beginning of the intervention. Intervention effects on the measured variables will also be evaluated using appropriate statistical tests based on the type of variable distribution. Potential consequences of the study might be the improvement of the measured variables in the intervention group compared to that of the control group. The expected results are that the intervention may significantly improve the status of the measured variables in the intervention group compared to that of the control group. If the outcomes of the intervention group do not change significantly compared to those of the control group, it can be due to different reasons. However, this can most likely be attributed to incorrect or insufficient use of the application by patients.

*Trial registration*: This protocol is registered in the Iranian registration of clinical trial (IRCT) on November 7, 2020 with the code IRCT20201015049037N1. URL: https://irct.ir/trial/51674

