#### Data collection

The required data will be collected using valid and reliable questionnaires that are introduced as follows. Data will be collected in three stages: prior to intervention (before the intervention and at the time of discharge), two months after the intervention and three months after the intervention (in the doctor's office or in the hospital outpatient clinic). Data from National Institute of Health Stroke Scale (NIHSS) and Barthel Index (BI) questionnaires and stroke complication checklist will be filled out by the attending neurologist and other questionnaires will be filled out by patients as self-report. Completion of questionnaires by patients will be done electronically and sent online through the application. Therefore, this survey will be considered as a “closed survey” since only registered users with a valid account can access the questionnaires and submit them. Application features will be inactive until patients, complete questionnaire items. After completion, application features will be activated and the questionnaire will be deactivated to prevent response duplications. The questionnaires will be reactivated two months and three months later. In order to ensure that no data will be missing, all fields and questions will be defined as mandatory in electronic questionnaires and patients will be warned to answer all questions before sending the questionnaire.

All online questionnaires will exactly be designed the same as paper questionnaires in terms of appearance, content and sequence of questions. That is, all the questions will be placed consecutively and not on separate pages. Therefore, it can be said that the validity and reliability reported for the paper version of questionnaire will also apply to the electronic version.

It is expected that the use of this application can improve the measured variables in the intervention group compared to the control group. Specifically, the research hypotheses are that patients in the intervention group have significant differences with those in the control group in terms of indicators of physical activity, depression, quality of life, medication adherence, satisfaction with treatment, and the number of complications.

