##### Complications

To assess the frequency and type of complications in patients, a stroke complication checklist will be used which includes a total of 19 complications, eight of which are based on the most common stroke complications from the perspective of the American Heart Association (AHA) and the American Stroke Association (ASA) [38] and 11 of which are based on the most common complications reported in related studies [39–42]. This checklist will be prepared by the researchers and the face and content validity of this checklist will be confirmed by 3 neurologists.

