#### Data analysis

Data analysis will be performed using IBM SPSS 22 [43]. The data will be entered anonymously using codes and numbers, which can be decoded only by one of the researchers (except the assessor or the analyst). The data will be stored in this software application and supported by a backup on another system kept in another place. The data will be first presented in the form of descriptive statistics and frequency distribution tables. The normality of the data will be checked using the Kolmogorov–Smirnov test. Depending on the type of data distribution, the mean or median of the data will be used as a criterion. In case of normal distribution of data, the mean will be used and in case of abnormal distribution (non-parametric), the median will be used for statistical calculations. In order to determine the relationship between the scores of patients’ activities of daily living, quality of life, depression, medication adherence and patient satisfaction with patients’ group type (control or intervention), an independent t-test will be used. If there is a significant difference between the intervention group and the control group, the effect of the intervention will be specified. Repeated measures analysis of variance (ANOVA) will also be used to analyze multivariate and control the effects of confounding variables on dependent variables. Confounding variables will include: patient age, sex and educational level, which can affect the final results. In all tests, a significance level of 0.05 will be considered. Pearson or Spearman correlation coefficient (according to the type of variable distribution) will be used to determine the relationship between the usage duration of the program and the score of the measured variables. After categorizing the time of application usage, one-way ANOVA or Kruskal–Wallis’s test (depending on the type of variable distribution) will be used to determine the relationship between the measured variables and the time of application usage. Chi-square test will be used to determine the relationship between the type of complications in both groups. Also, to determine the relationship between the scores of the measured variables before and after the intervention, a paired t-test will be used in each group separately. Hypothesis H0 will indicate the absence of correlation and Hypothesis H1 will indicate the existence of correlation between the measured variables.

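### The hypothesis concerns the number of complications, but the only test that names complications is a chi-square on their type

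*Protocol article*

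**What the plan says.** Three places in the protocol article make the number of complications an outcome:

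- The abstract's Discussion paragraph lists "the number and type of complications in patients in two groups" among the outcomes to be assessed.
- The Data collection section gives the research hypotheses. The between-group differences expected there end with "medication adherence, satisfaction with treatment, and the number of complications".
- The Complications section gives the purpose of the instrument, "To assess the frequency and type of complications in patients", and its length: "a stroke complication checklist will be used which includes a total of 19 complications".

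The Data analysis section names complications once: "Chi-square test will be used to determine the relationship between the type of complications in both groups". The independent t-test between groups is assigned to named outcomes, "activities of daily living, quality of life, depression, medication adherence and patient satisfaction", and a complication count is not one of them. Repeated measures ANOVA "will also be used to analyze multivariate and control the effects of confounding variables on dependent variables", without saying which variables these are. The same section sets a significance level of 0.05 for every test.

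**The concern.** A hypothesis about how many complications occur needs a test that compares how many occur. The test named for complications compares what kind they are, which is a different question. The Data analysis sentence also does not say what table the chi-square is run on. Two readings are natural:

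- one pooled table of group by 19 types;
- nineteen 2×2 tables, one for each complication present or absent.

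Neither tests the number per patient, and they fail in different ways. On the pooled reading, an even reduction across all types could be reported as no difference. On the per-type reading, one chance result among 19 could be reported as an effect. An analyst who follows the section literally would have no p-value or estimate for the hypothesis as stated.

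**Working it through.** **The plan's own figure.** The article gives no figure for complications. Its sample size is for NIHSS (Study design and setting): 2 × 8² × (1.96 + 1.282)² / (12 − 5)² = 128 × 10.51 / 49 = 27.46, against 27 stated. The figure reproduces but has no bearing on complications.

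**Which analysis covers the count?** Taking the Data analysis section in turn:

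| Planned analysis | Covers the number of complications between groups? |
|---|---|
| Independent t-test | No; five outcomes are named and this is not one |
| Repeated measures ANOVA | Unclear; dependent variables are not named |
| Correlation, one-way ANOVA, Kruskal–Wallis | No; these relate outcomes to application usage |
| Chi-square | Type only |
| Paired t-test | No; within each group |

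**Reading 1: one group-by-type table.** The expected count is row total × column total / grand total. As an illustration, let five types occur 30, 20, 20, 10 and 10 times in the control group (total 90), and let the application halve each: 15, 10, 10, 5 and 5 (total 45). For the first type the expected counts are 90 × 45 / 135 = 30 and 45 × 45 / 135 = 15, exactly as observed. The same holds in every column, so chi-square = 0 and p = 1. A simple Poisson comparison of the totals gives z = (90 − 45) / √135 = 3.87. This is algebra and does not depend on the rates chosen. In addition, a patient with several complications enters such a table several times, which breaks the independence that the test assumes.

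**Reading 2: one 2×2 test per type.** Each patient contributes one yes or no to each table, and each table responds to a change in incidence. With 19 independent tests at 0.05, the chance of at least one false positive is at most 1 − 0.95¹⁹ = 0.62.

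**Simulation.** Complication rates are not in the article, so these inputs are assumed: 30 patients per arm, 19 independent yes/no items of unequal frequency, and a control mean of 1, 2 or 3 complications per patient. The effect is either none or a halving of every type. There were 1,000 trials per scenario; the 2×2 tests have no continuity correction. Entries are the percentage of trials that reject.

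| Control mean | Effect | Pooled chi-square | Mann–Whitney on count | t-test on count | At least one of 19 tests |
|---|---|---|---|---|---|
| 1 | none | 0.8 | 5.5 | 5.8 | 37.1 |
| 1 | halved | 1.1 | 59.8 | 63.0 | 56.4 |
| 2 | none | 0.9 | 4.8 | 4.3 | 52.8 |
| 2 | halved | 1.4 | 92.1 | 93.6 | 86.7 |
| 3 | none | 0.5 | 5.4 | 5.1 | 60.7 |
| 3 | halved | 0.9 | 98.9 | 98.8 | 96.3 |

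Sensitivity, with a control mean of 2.05:

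- With extra between-patient variation, the power of Mann–Whitney on counts falls from about 90% to about 70%. The pooled chi-square stays at about 1–2%.
- With Yates correction, the family-wise error of the 19 tests falls to about 17–20%.
- With Bonferroni adjustment (control means of 1, 2 and 3), the chance of detecting any single type when all are halved is about 3%, 16% and 34%.

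**The case against.** The strongest reply is that the text never specifies a pooled table. With a checklist, presence or absence of each item by group is at least as natural. On that reading the near-zero chi-square does not arise, and neither does the dependence between entries. A reader might infer that a real reduction would necessarily be missed. The article does not support that: under the assumed rates, at least one of the 19 unadjusted tests rejects in 56–96% of trials when every type is halved. Those rejections come with a 37–61% rate under no effect and concern single types, so they do not replace a test of the number.

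A reader might also infer that the reported p-values would be invalid. That too goes too far. The pooled test, in these simulations, is conservative (0.5–0.9% under no effect), so it loses power but does not create false positives. The per-type problem is multiplicity across tests, not the validity of each one. The 62% figure is an upper bound; sparse items and continuity correction bring the simulated values down to between 17% and 61%.

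Finally, the ANOVA on unnamed dependent variables could be stretched to include a complication count. The text does not say so, and the t-test sentence, which does name its outcomes, leaves the count out. It is therefore accurate to say that the chi-square is the only test naming complications, but not that no other analysis could ever cover them.

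Nor is this merely detail left to a fuller document. The article states the hypothesis and names a test for complications, and the two do not match.

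**Conclusion.** The point holds in a limited form. The hypothesis in Data collection concerns the number of complications, the only test in Data analysis that names complications concerns their type, and no between-group test is clearly assigned to the count. That mismatch rests on the text alone.

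Its size depends on the reading:

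- **Pooled table:** a proportional reduction in all types gives a chi-square near zero. Rejection is about 1–2%, against roughly 60–99% for a count test.
- **Per-type tests:** there is still no test of the number per patient, and family-wise error is roughly 17–61%.

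The p = 1 result for a proportional reduction needs no assumed rates. Every percentage does: it rests on assumed complication frequencies, 30 patients per arm and, for power, a 50% reduction in every type. Complications are one of several outcomes and not the one used for the sample size, so the point should be corrected but does not undermine the trial as a whole.

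**What to change.** In Data analysis, name a between-group comparison of the number of complications per patient (0–19, counting each checklist item once) at a stated assessment as the test of the hypothesis in Data collection. A Mann–Whitney test with an effect estimate and 95% confidence interval is enough; a count model giving a rate ratio is an option, not a requirement.

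Report each complication type as the number of patients affected per arm, with Fisher's exact or chi-square tests labelled descriptive. Do not use a pooled type-by-group chi-square. If the repeated measures ANOVA was meant to cover the count, say so.

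The cost is a change of analysis wording. The same checklist data are used, with no extra patients, visits or measurements.

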## Discussion

Various protocols have been designed to evaluate the impact of mobile applications and trainings on the outcomes of patients with stroke [44–47]. However, these studies differ in terms of sample size, number of variables and outcomes to be measured, duration of intervention and protocol design. In Iran, a study in which first an application is designed using expert and patient needs assessments according to a standard guideline and then the impact of designed application on patients with stroke is evaluated has not been done yet. In other foreign studies, less attention has been paid to different aspects of ICF. However, in the present study, we will try to evaluate the outcomes based on valid and reliable questionnaires that are related to different sections of ICF.

In addition to providing educational materials via text and image, the application will provide appropriate exercises using educational video clips. It will also contain items such as reminders and warnings to take medications and doctor's appointments, the possibility of communicating with the therapist via chats, voice calls or video calls, the possibility of weekly goal setting, and writing notes related to the rate of goal achievement. It is expected that the use of this application will potentially improve and enhance the motor function of the upper and lower limbs, balance and walking, social participation and self-efficacy in the intervention group more than those of the control group. In similar studies [48–50], the positive effects of mobile applications on improving the motor function of limbs after stroke have been shown. However, some other studies [51, 52] have reported the use of this type of intervention on the motor function of the limbs without significantly improved effects. The reasons for this difference can be related to various factors such as the context of the society under study, the mobile application used and its capabilities, the duration of the intervention and the level of patient cooperation to use the application.

All instructions and exercises in the application will be approved by the experts to be considered safe for patients to minimize the possibility of causing harm. To eliminate the risk of possible harm to patients during exercise, they will be advised to start the training with an easy level and to make sure that the exercises are done in the presence of a caregiver, and that the way to receive support from a caregiver is fully taught in the application through videos. All of the ethical considerations in clinical trials (including Helsinki ethical codes) will be considered by researchers. If medical complications arise during the study; patients will be treated for free by the responsible physician. Compensation in this regard will be done according to the laws of the Medical System Organization.

For auditing the trial, after registering each sample, a researcher will monitor the patient registration process and assign them to either the control or intervention group using the admin-side application. The completion of questionnaires by patients will also be monitored by this person. If the questionnaires are not filled out, patients will be reminded though a phone call. Filling out the questionnaires will be audited two and three months after patient registration and the necessary actions will be done in case of possible delays. These actions will include sending reminders through the application, sending messages and making phone calls.

The most important limitation of this study is the possibility of lack of cooperation of some patients to participate in the study. Researchers will understand the specific conditions of patients with stroke and will fully explain the purposes of the study to them, but in any case, if patients, despite being informed about the goals and efforts of researchers to obtain their satisfaction, seem to be unwilling to participate in the study, according to the principle of informed and free consent, they will be excluded from the study at any time during the research. Another limitation is the lack of qualified patients at the study site, which will probably make the sampling longer, but will not harm the results of the study. However, larger trials with larger samples in centers with more patients are recommended. One of the operational problems in studies of this type is the possibility of patients not being able to work with smartphones. If the patient is not able to work with a smartphone, his/her caregiver will be consulted. Of course, this person needs to be someone such as a patient’s wife/husband or child who is always available to the patient.

It can be said that the most important strength of this trial is the development of an application based on the needs assessment of all stakeholders. This can be a great advantage over studies that use an off-the-shelf application because it will be designed and adapted to the needs of the population under study.

The ability to generalize the results of the study to similar populations should be somewhat cautious. Although the sample at of this study is based on the formula and data obtained from previous studies, it is nevertheless a relatively small sample. Therefore, the generalizability of the results of this study needs to be done with caution.

### Trial status

Expected recruitment start date is April 2022 (after the manuscript submission date) and the recruitment will be completed approximately in September 2022. Possible changes related to the protocol will be transferred to the Iranian Registry of Clinical Trials (IRCT) System and the necessary changes will be made and informed on that website.

## Data Availability

The datasets used and/or analyzed during the current study are available from the corresponding author on reasonable request.

## Abbreviations

AHA: American Hospital Association
ANOVA: Analysis of Variance
ASA: American Stroke Association
AU: Attribute of Usability
BDI: Beck Depression Index
BI: Barthel Index
CVI: Content Validity Index
CVR: Content Validity Ratio
CW: Cognitive Walkthrough
EQ-5D-3L: EuroQol group-5 Dimensions-3 Levels
ICF: International Classification of Functioning, disability and health
MMAS-8: Morisky Medication Adherence Scale-8 items
NIHSS: National Institute of Health Stroke Scale
